**Outcomes and minimum meaningful differences**

We anticipate enrolling 200 patients per clinic with 9 clinics per condition (3 per condition per country), for a total of 18 clinics and approximately 3600 patients (at least 2520 retained at 12 months). Power calculations demonstrate that this number of participants will allow us at least 80% power to detect a 25% relative difference between conditions for the primary outcome variable of any unprotected sex during the past 3 months, allowing for up to 30% loss to follow-up.

**Training for all study personnel**

The design of this project requires that the project staff at each study site have clear, defined roles and work cooperatively. Figure 2 below shows a sample country project staffing diagram and the staff duties are discussed in the text that follows.

**Figure 2. Sample country staffing diagram.**

**Country Project Team / Investigators**

**Site Evaluation Coordinator**

**(1 per project site,**

**6 total)**

**Country Project Coordinator**

**(n = 1)**

**Interviewers**

**(2 per project site,**

**12 total)**

**Health Care**

**Providers**

**(Clinic staff, not study staff)**

**Lay Counselors**

**(2-4 per project site,**

**12-24 total)**

**Data Entry Staff**

**(n = 1-2)**

**Site Program Coordinator**

**(1 per intervention site, 3 total**

**6 total))**

*Roles and responsibilities of project staff*

There will be one Country Project Coordinator for each of the countries who will oversee operations at all of the sites in their country. They will visit each participating clinic site at least once per month and troubleshoot and monitor project progress as needed. They will supervise Site Evaluation Coordinators and also manage quality control for data collection. The Country Project Coordinator will provide in-country technical assistance for study data collection issues to the clinic. In addition, the Country Project Coordinator will ensure that data from each site are sent to a central location and will supervise data entry staff, who are responsible for entry of all data from all the clinics in their country. Once data are entered and checked, the data entry staff will transmit the data using the Secure Data Network to CDC-Atlanta weekly..

The Site Evaluation Coordinator will oversee all study evaluation activities at the clinic site. They will supervise data collected by interviewers, ensure interviewers meet responsibilities and goals, collect data from health care provider and lay counselor observations, extract data from patient charts, gather information on clinic services provided, serve as a backup interviewer, and will be responsible for all study and data collection deadlines.

The Site Program Coordinator will be an existing full-time clinic employee (e.g., a nurse or matron, if possible) with approximately 25-50% of their time dedicated to this project. They will oversee implementation of the intervention package by health care workers and counselors at their respective clinic, supervise counselors (where appropriate) to ensure responsibilities are being conducted according to project implementation guidelines, maintain commodities and other needed supplies for project implementation, and assist in record keeping and clinic level data collection. In addition, the Site Program Coordinator will be the primary contact at the clinic for program-related intervention issues; communicate with clinic administration, clinic staff, project coordinator and study team regarding project-related issues; and ask about, address, and report all adverse events associated with the intervention package to the Country Project Coordinator and CDC-Atlanta immediately.

Counselors will be hired by the project to work as part of the clinical team in the HIV clinic. Their main duties will be to conduct group education sessions, individual and couple counseling with HIV-infected clinic patients, and HIV counseling and testing (where allowed by national guidelines) with partners of clinic patients. Also, they will communicate with health care providers and other clinic staff as needed about patient care and referrals and discuss any intervention concerns or patient issues with the Site Program Coordinator.

The project interviewers will collect data from patients, health care providers, and lay counselors. The interviewers will ensure that data collection activities adhere to the study protocol, that the data collected are complete and of the highest possible quality, and that all activities are conducted in a professional manner. Interviewers will complete participant informed consent, conduct patient interviews, administer questionnaires to health care providers and lay counselors, and assist the site evaluation coordinator at the clinic with other parts of the study including following-up and tracking study participants.

*Training for project staff*

Interviewers will receive thorough structured training from project staff on all the data collection forms and procedures. Training agenda items include purpose and scientific objectives of the project, interviewer responsibilities, locating and contacting participants, participant’s rights and informed consent, and confidentiality requirements. The hands-on training will include an introduction to data collection forms and procedures, working through several mock interviews, and completing administrative forms and reporting work progress. Training for interviewers is expected to take approximately 16 hours per interviewer and an additional 8 hours is estimated for follow-up training.

The bulk of the hands-on training, and the most crucial component, will be the mock interviews, and project staff will act as both the trainer and the mock respondent. The trainer will take the interviewers through each step of the interviewing process, from enrolling participants to ending the interview and completing any necessary forms. Within the interview itself, the trainer will demonstrate both the interviewing task being required of them as well as the response task being required of the project participant. Question-by-question instructions and the use of any visual or recall aids will be reviewed.

The trainer will also ask questions of the interviewer or intentionally make mistakes similar to those the interviewers may encounter in a real interview thus requiring the interviewer to learn how to handle unusual circumstances. Also, interviewers will be trained to refer that day to clinic and community counselors and health care providers any patient who displays obvious signs or endorses significant experience of depression or alcohol abuse. However, the project interviewers are not trained mental health professionals and the questionnaires are not diagnostic tools; thus, interviewers will not be responsible for providing any psychological services to patients or for articulating specific concerns or diagnostic impressions related to the referral.

The multilingual interviewers will work though additional mock interviewers in other languages to become familiar with the non-English versions of all the assessments and to discuss and resolve any issues specific to interviewing project participants at their site in languages other than English.

In addition to this type of mock interview, the interviewers will be paired together with each taking a turn at interviewing their partner. This method more closely resembles an actual interview and the performance of each interviewer can be more carefully monitored as the trainers walk around to observe and provide individual instruction.

During this training, the trainers will have ample opportunity, particularly through mock interviews, to work directly with each interviewer. In the context of these interactions, trainers will qualitatively ascertain the interviewer’s skills. At the end of training, any interviewer the trainers or other project staff believe may have difficulty with the project interviewer tasks be asked by project staff to not continue work with the project.

Interviewers will receive a Field Operations Procedures Manual which will serve as a procedural guide during actual data collection.

**PROCEDURES/METHODS: DATA HANDLING AND ANALYSIS**

**Data analysis plan**

The proposed project will be a multi-site nested cohort group-randomized trial (GRT) with a-priori matching at the clinic level. Here, group refers to clinic, and “study condition” or “condition” will refer to intervention vs. control assignment. Matching of clinics will be performed in the design of the project to improve balance across study conditions on factors potentially related to the outcome variables. However, the matching will not be reflected in the analysis, as studies have shown that doing so often reduces power in smaller GRTs due to the loss of degrees of freedom (Diehr et al., 1995). Site (country) will be reflected in the analysis, both as an interaction with intervention effect to test for a differential intervention effect by site, and as a main effect to adjust for pre-intervention differences in the outcome variables of interest. If interactions between site and the intervention effect are statistically significant, we will explore intervention effects within country. However, power will be low for this test as the sample sizes within countries are small.

This project presents a number of challenges that must be addressed in the primary and secondary analyses. First, the analytic approach must take into account the correlation among patients within clinics and multiple measurements on the same participants within the same groups over the course of the project. Second, as with any longitudinal cohort study, there is potential for attrition over the course of the study and differential attrition between intervention and comparison conditions. Finally, many of the outcome measures used to assess the impact of the intervention will be non-normally distributed, including dichotomous indicators for whether risky sexual behaviors occurred and frequency variables indicating how many partners a participant reported.

Prior to beginning analyses to evaluate intervention effects, preliminary analyses will be conducted to determine whether randomization was successful in creating equivalent groups of participants across study conditions at baseline. Any differences between intervention and comparison conditions at baseline will be controlled for in subsequent evaluations of the intervention effect. Analysis will also be conducted for the purpose of describing the baseline sample and examining the distributions of each of the outcome variables. Further analyses will explore distributional assumptions related to each outcome measure.

For the main outcome analysis, numerous options are available for the test of the effectiveness of the intervention. Mixed-model regression methods are often used for the analysis of GRTs and easily accommodate the over-time correlation at the group and member level, as well as the correlation of observations within groups. Using different procedures within SAS, such as PROC MIXED, PROC GLIMMIX, and PROC NLMIXED, mixed-model regression can be performed for many common statistical distributions, and some less-common ones often used in HIV research (e.g., censored log-normal for viral load measurements). We propose to use mixed-model regression methods to test for a difference between study conditions at 6 and 12 months, incorporating the baseline measurement as a covariate. Initial models will include fixed effects for the baseline value of the outcome variable, country, study condition, time (6 or 12 month measurement), the country by study condition interaction, the time by study condition interaction, the time by country interaction and the three-way interaction between time, study condition and country. Models will also include random effects for group and group by time. If the country by time by condition interaction is significant, the time by condition interaction will be tested stratified by country to determine the pattern of intervention effects for each country separately. Because power is based on the number of clinics, however, tests for country differences will have low power relative to the overall test for an intervention effect. If the three-way interaction is not significant, it will be dropped from the model and further evaluation of intervention effects will focus on the time by condition term. If this term is significant, condition effects will be evaluated stratified by timepoint; if it is not significant, a pooled estimate of the intervention effects (across timepoints) will be computed. This effect estimate has the advantage of greater power than a test at either timepoint alone, due to the larger number of observations. The random effects for group and time by group will control for the correlation within participant over time in these models. Also, the country by condition effect will be tested to determine whether the study condition effect (pooled across time) differs by country.

In addition to the approach we propose, a variety of other analytic approaches have been used for GRTs, including permutation tests, generalized estimating equations (GEE), and random coefficients models. Permutation tests involve computing a summary statistic for the differences between conditions and comparing this summary statistic to a distribution of all possible such statistics given the design of the study. We chose not to employ this method because, with three timepoints, we would either need to do two separate permutation tests with an alpha correction for multiple hypothesis tests, or do a permutation test on the group-specific slopes over time. The first approach would likely be less powerful than the one we chose, and the second approach would express intervention effects as linear terms, and the approach we chose allows for a nonlinear pattern of intervention effects over time. We avoided using a GEE approach because several simulation studies have shown GEE to yield an inflated Type I error rate in GRTs with fewer than 20 groups per condition (Murray, Hannan, & Baker, 1996; Feng, McLerran, & Grizzle, 1996). We also chose not to employ a random coefficients model approach because intervention effects are specified as linear trends in the random coefficients model and we have little prior evidence on which to base assumptions about the pattern of intervention effects.

The main outcome analysis will use an intent-to-treat approach (i.e., each participant will be analyzed in the study condition to which he or she was randomly assigned). Secondary analyses will explore the impact of actual intervention received, which will vary across participants. These analyses will need to control for or stratify by participant ARV status as those on ARVs will likely have more contact with providers.

Following the analysis of the observed data, we will repeat the primary outcome analysis using multiple imputation to address the potential for bias due to missing data. Multiple imputation ‘fills in’ the missing data using the association between variables in the dataset, and reflects the uncertainty in the imputed values by basing variance estimates on between- and within-imputation variability. This project is likely to have a moderate amount of missing data, and ignoring this missingness may lead to bias in the estimates of the intervention effect.

Tables 3 and 4 below provide sample table shells for the outcome analyses.

Table 3. Sample outcome analysis table shell indicating percentages for primary outcome variable by study condition and data collection period.

|  | Baseline  N (%) | | 6-Month Follow-up  N (%) | | 12-Month Follow-up  N (%) | |
| --- | --- | --- | --- | --- | --- | --- |
| Variable | Intervention  (n=) | Comparison  (n=) | Intervention  (n=) | Comparison  (n=) | Intervention  (n=) | Comparison  (n=) |
| Any unprotected sex past 3 months |  |  |  |  |  |  |
|  |  |  |  |  |  |  |
|  |  |  |  |  |  |  |
|  |  |  |  |  |  |  |
|  |  |  |  |  |  |  |
|  |  |  |  |  |  |  |
|  |  |  |  |  |  |  |
|  |  |  |  |  |  |  |

Table 4. Sample outcome analysis table shell indicating odds ratios and 95% confidence intervals for primary outcome variable by study condition and data collection period.

|  | Baseline  OR (95% CI) | | 6-Month Follow-up  OR (95% CI) | | 12-Month Follow-up  OR (95% CI) | |  |  |
| --- | --- | --- | --- | --- | --- | --- | --- | --- |
| Variable | Intervention | Comparison | Intervention | Comparison | Intervention | Comparison | 2 | p-value |
| Any unprotected sex past 3 months |  |  |  |  |  |  |  |  |
|  |  |  |  |  |  |  |  |  |
|  |  |  |  |  |  |  |  |  |
|  |  |  |  |  |  |  |  |  |
|  |  |  |  |  |  |  |  |  |
|  |  |  |  |  |  |  |  |  |
|  |  |  |  |  |  |  |  |  |

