**Study design and locations**

Study design

This project will be a longitudinal group-randomized trial, randomized at the clinic level. Six HIV care and treatment clinics in each of three countries (Kenya, Namibia, and Tanzania) will participate (18 clinics total). The six clinics in each country are matched based on size, health care provider/patient ratio, and services provided (e.g., number of health care providers, size of clinic and number of HIV-positive patients seen, level of care provided). Intervention status was randomly assigned to one clinic in each matched pair.

Health care providers and staff will be trained to deliver the HIV prevention interventions to all patients in clinics randomly assigned as intervention sites. In the comparison site clinics, providers and staff will deliver their usual standard of care services. Following completion of the project, health care providers in the comparison clinics will be trained to deliver the HIV prevention interventions.

A measurement cohort of 3600 HIV-positive patients will be randomly recruited to participate from each of the 18 clinics in the 3 participating countries (n=200 per clinic). Participants in the intervention and comparison groups will be assessed at 3 time points: Baseline (enrollment), 6-, and 12-months. After participants have completed the baseline assessments, the prevention interventions will be implemented by health care providers and lay counselors in the intervention clinics.

Assessment of patients will include completion of an interviewer-administered questionnaire. At each assessment, trained interviewers will ask participants about their sexual behavior, STI symptoms, pregnancy status and intentions, contraceptive use, alcohol use, HIV ARV medication adherence and adherence to co-trimoxazole prophylaxis, partner HIV testing history and HIV status, mood and perceived social support (see Appendix H). To the extent possible, participants will be interviewed following a routine HIV clinic visit in order to reduce burden on patients.

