**Sampling, including sample size and statistical power**

Participants will be sampled from the database of patients already receiving care at the project clinics. Information about gender, whether on ART, and last clinic visit will be used to create a list of potential participants. From that list, patients will be randomly selected to create a list of patients to approach about participating in the project. When patients arrive at the clinic the list will be checked and if their name is on it they will be asked if they are interested in participating in the project (see enrollment section below for further description). If they are not, their name will be removed from the list. Each clinic will enroll approximately half of each gender and half who are on ART. A tally of persons in each of the gender by ART cells will be kept updated daily. As each of the cells near the enrollment targets the study coordinator will monitor the potential participant list to ensure that appropriate numbers of participants are in each group.

The primary outcome variable for the project will be participant self-report of any unprotected sex in the past 3 months. Prior studies have found rates of condom use to be very low in the areas in which this project will be conducted (Arthur et al., 2007; Feldblum et al., 2000; Kapiga et al., 2006; Mwaluko et al., 2003; Norman, 2003; Stanton et al., 1999; Ross et al., 2007; Watson-Jones et al., 2007). We will assume a rate of at least 50% for any unprotected sex in the past 3 months in the comparison condition for sample size estimation.

Although the proposed project includes measurements at three time points (baseline, 6 months and 12 months), sample size estimates are presented for the simple difference between proportions in the two project conditions at the 12-month follow-up only. This approach is conservative because analytic approaches taking into account the multiple observations on each participant will be more powerful. We use the cross-sectional approach for sample size estimation because no prior data are available on which to base prediction of the pattern of intervention effects over time and the magnitude of the over-time correlation of groups and group members that we can expect in this project. Our sample size estimates do take into account expectations of attrition in the project cohort, which we expect to be moderate (at most 30% at the 12-month follow-up).

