**Table 1. Number of groups and members per condition needed for at least 80% power to detect a 20-30% difference between intervention and comparison conditions in report of any unprotected sex in the past 3 months (assuming intraclass correlations of 0.01 or 0.02).**

| **P1** | **P2** | | **ICC** | **Absolute Difference** | **% Difference** | **Members per group enrolled** | **Members per group retained** | **Number of groups needed per condition** |
| --- | --- | --- | --- | --- | --- | --- | --- | --- |
| .50 | .3875 | | .01 | .1125 | 22.5 | 200 | 140 | 7 |
| .50 | .3750 | | .01 | .1250 | 25 | 200 | 140 | 6 |
| .50 | .3625 | | .01 | .1375 | 27.5 | 200 | 140 | 5 |
| .50 | .3500 | | .01 | .1500 | 30 | 200 | 140 | 4 |
| .50 | | .3750 | .02 | .1250 | 25 | 200 | 140 | 9 |
| .50 | | .3625 | .02 | .1375 | 27.5 | 200 | 140 | 7 |
| .50 | | .3500 | .02 | .1500 | 30 | 200 | 140 | 6 |

P1=proportion reporting any unprotected sex in the comparison group; P2=proportion reporting any unprotected sex in the intervention group

Table 1 shows that with 9 clinics per condition, each with 200 patients enrolled, the project would have at least 80% power to detect a 25% difference between intervention and comparison (absolute difference of 12.5%) with an ICC of 0.02. If the ICC is smaller or the intervention effect larger, power will be greater then 80%.

Summary

We anticipate enrolling 200 patients per clinic with 9 clinics per condition (3 per condition per country), for a total of 18 clinics and approximately 3600 patients (at least 2520 retained at 12 months). Power calculations demonstrate that this number of participants will allow us at least 80% power to detect a 25% relative difference between conditions for the primary outcome variable of any unprotected sex during the past 3 months, allowing for up to 30% loss to follow-up.

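### Additional covariates in the main model are chosen by observed baseline imbalance instead of being named in advance for their prognostic value

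*Protocol*

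**What the plan says.** The Data analysis plan first announces that "preliminary analyses will be conducted to determine whether randomization was successful in creating equivalent groups of participants across study conditions at baseline". It then fixes the consequence: "Any differences between intervention and comparison conditions at baseline will be controlled for in subsequent evaluations of the intervention effect". The wording is mandatory, and it covers every later evaluation of the effect, so it includes the main outcome analysis. It gives no candidate list, no definition of a difference, no unit of comparison and no limit on the number of covariates.

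The same section does fix a core mixed model in advance: baseline value of the outcome, country, condition, time (6 or 12 months) and their interactions, with random effects for clinic and clinic by time. The covariates found at baseline come on top of this core.

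Three other statements bear on the point:
- Study design and locations: "Intervention status was randomly assigned to one clinic in each matched pair".
- Sampling, including sample size and statistical power: "Each clinic will enroll approximately half of each gender and half who are on ART", with the gender-by-ART cells tallied daily.
- Data analysis plan: the matching is left out of the analysis because including it "often reduces power in smaller GRTs due to the loss of degrees of freedom".

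**The concern.** How far a covariate differs between arms says nothing about whether it predicts unprotected sex. A rule that adjusts for whatever differs therefore uses the wrong criterion. It can admit irrelevant variables, and it can leave out relevant ones that happen to be balanced.

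The protocol's own sampling makes the second failure likely. Gender and ART status are held near half and half in every clinic, so a baseline comparison will rarely flag them. Yet the protocol treats ART status as important. Under Estimated number of participants, the sample is split by ART because patients off ARVs are thought healthier and more likely to be sexually active. Under HIV Prevention Interventions, patients on ART are expected to receive the intervention 4 to 12 times, against about 4 times for the others. The Data analysis plan requires ARV status to be handled in the secondary exposure analyses, but not in the main one.

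At stake are a primary model that is only partly fixed beforehand, and some precision in a trial of 18 clinics.

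**Working it through.** **Inputs from the protocol** (Sampling, including sample size and statistical power): 9 clinics per condition; 200 enrolled and 140 retained per clinic; 0.50 against 0.375; ICC 0.01 and 0.02; two-sided alpha 0.05. **Assumptions, not in the protocol:** 20 independent candidate variables; a difference means p<0.05; the simulation settings in steps 3 and 4.

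**1. The plan's own figure.** Variance of the difference at ICC 0.02 = (0.50×0.50 + 0.375×0.625) × (1 + 139×0.02) / (140×9) = 0.484375 × 3.78 / 1260 = 0.001453, so SE = 0.0381 and 0.125/0.0381 = 3.28. With 2×(9−1) = 16 df the critical t is 2.12, and power is P(T < 3.28 − 2.12) = 0.868. The stated 80% or more reproduces, as does 3600 × 0.70 = 2520.

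**2. How many chance covariates the rule admits.**
- Clustering respected: 20 × 0.05 = 1 expected; P(at least one) = 1 − 0.95^20 = 0.64.
- Clustering ignored, 200 per clinic: the design effect is 1 + 199×0.01 = 2.99 or 1 + 199×0.02 = 4.98. The false-flag rate per variable is 2×[1 − Φ(1.96/√DE)] = 0.257 or 0.380. Over 20 variables that is 5.1 or 7.6.

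**3. Type I error.** A clinic-level null simulation (18 clinics, 3 countries, 4000 runs per setting, 10 or 20 candidates, 3 of them given a correlation r with the outcome) rejected in 0.030 to 0.053 of trials when covariates were selected on imbalance. There is no inflation. Rejection reached 0.057 to 0.078 only when either the adjusted or the unadjusted result was allowed to count.

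**4. Precision.** SD of the effect estimate in the same simulation, 10 candidates, clustering respected:

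| r of each of the 3 covariates | Country only | Selected on imbalance | The 3 named in advance |
|---|---|---|---|
| 0 | 0.466 | 0.527 | 0.537 |
| 0.3 | 0.462 | 0.514 | 0.454 |
| 0.5 | 0.470 | 0.476 | 0.269 |

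Selecting on imbalance did not improve on country alone in any row. Naming covariates helps only as far as they predict the outcome. The simulated covariates are clinic-level and the reference model omits the baseline outcome, so these gains should not be read across to this trial.

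Gender and ART status are balanced within clinics, so they can remove only within-clinic variation. On the proportion scale its share of a clinic mean's variance is [(1 − ICC)/140] / [ICC + (1 − ICC)/140]: 0.00707/0.01707 = 41% at ICC 0.01, and 0.0070/0.0270 = 26% at ICC 0.02. If the two variables explain a fraction R² of that variation, the variance of the effect falls by about 0.41×R² or 0.26×R². The protocol gives no R², so the gain is bounded but not known.

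**5. Degrees of freedom.** These are lost only to clinic-level covariates. With country fitted (14 df) power is 0.862. Adding 5 clinic-level covariates that bring no precision gives 0.832, and adding 8 gives 0.781. With country by condition fitted there are 18 − 6 = 12 df and power 0.854; four such covariates leave 8 df and 0.821.

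**The case against.** The strongest defence is that the rule looks only at baseline data, before effects are evaluated. Intermediate reviews and analyses confirms that follow-up data are not examined for effects during the project and that analysis code is written before data collection ends. The main prognostic terms are already fixed, and the screening details could sit in an SAP. All of this stands, but it does not reach the criterion itself. An SAP could add a test or a threshold and the rule would still select on imbalance.

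Four stronger readings are tempting, and the documents do not support them:
- *The stated error rate fails.* It does not (step 3). The higher rejection figures need an analyst free to report the better of two models, and the protocol offers no such choice.
- *Five to eight chance covariates should be expected.* That needs a participant-level test that ignores clinics. No test is stated, and the Data analysis plan requires the primary and secondary analyses to respect within-clinic correlation.
- *The rule breaks the power claim.* The comparison is of participants, and participant-level covariates do not each cost a clinic degree of freedom. Even four clinic-level covariates leave power above 80%.
- *Every baseline difference is chance.* Clinics are already assigned and listed by arm, while enrolment comes later in the Study timeline, so some differences may reflect recruitment. That justifies looking at imbalance, but not choosing the primary model by it.

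It is also fair to say that adjusting for gender and ART status, being near balance by design, is mainly a matter of precision and not of bias.

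**Conclusion.** The point holds in a limited form. The core of the primary model is fixed, but the additional covariates are chosen by observed imbalance, which is the wrong criterion. The model is not fully settled in advance, chance imbalances can enter, and two likely prognostic factors will usually stay out. Type I error is not inflated by the rule itself.

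The count of chance covariates (about 1 in 20, or about 5 to 8 under a screen that ignores clinics) rests on an assumed 5% threshold and 20 independent candidates. The precision forgone by omitting gender and ART status is real if they predict the outcome, but it is capped by the within-clinic share of variance and cannot be sized from the protocol. A change is worth making because the better rule costs almost nothing.

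**What to change.** Replace the sentence with a named covariate set for the primary outcome: baseline value of the outcome, country, gender and ART status at enrolment. Use the same set for other participant-level outcomes where each variable varies. Omit gender for urethral discharge, which concerns men only, and ART status for ARV adherence, which concerns those on ARVs. Use neither for clinic-level service counts.

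Describe baseline balance by condition without using it to select covariates. Report any further imbalance-adjusted model as a labelled sensitivity analysis; this also covers differences that arise from recruitment after clinic assignment.

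The cost is wording. Gender and ART status are recorded on the screening form, and the set can be locked when the analysis code is written, before follow-up outcomes are analysed. The one drawback is minor: an unexpected imbalance would be dealt with only in the sensitivity analysis.
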